## Abstract

**Background:**

Adolescent depression is a common mental health problem and there is an urgent need for effective and accessible treatments. Internet-based interventions solve many obstacles for seeking and receiving treatment, thus increasing access to effective treatments. Internet-based cognitive behavioural therapy (ICBT) for adolescent depression has demonstrated efficacy in previous trials. In order to broaden the range of evidence-based treatments for young people, we evaluated a newly developed affect-focused Internet-based psychodynamic treatment (IPDT) in a previous study with promising results. The purpose of the planned study is to evaluate the efficacy of IPDT for adolescent depression in a non-inferiority trial, comparing it to ICBT.

**Methods:**

The study will employ a parallel randomized non-inferiority design (ratio 1:1; *n* = 270). Eligible participants are adolescents 15–19 years suffering from depression. The primary hypothesis is that IPDT will be non-inferior to ICBT in reducing depressive symptoms from pre-treatment to end of treatment. Secondary research questions include comparing outcomes of IPDT and ICBT regarding anxiety symptoms, emotion regulation and self-compassion. Additional data will be collected to evaluate cost-effectiveness as well as investigating predictors, moderators and mediators of outcome. In addition, we will examine long-term outcome up to 1 year after end of treatment. Diagnostic interviews with MINI 7.0 will be used to establish primary diagnosis of depression as well as ruling out any exclusion criteria. Both treatments consist of eight modules over 10 weeks, complemented with therapist support through text messages and weekly chat sessions. Primary outcome measure is the Quick Inventory of Depressive Symptomatology in Adolescents Self-Rated (QIDS-A17-SR). Primary outcome will be analysed using data from all participants entering the study using a multilevel growth curve strategy based on the weekly measurements of QIDS-A17-SR. The non-inferiority margin is defined as *d* = 0.30.

**Discussion:**

This trial will demonstrate whether IPDT is non-inferior to ICBT in the treatment of adolescent depression. The study might therefore broaden the range of evidence-based treatment alternatives for young people struggling with depression. Further analyses of data from this trial may increase our knowledge about “what works for whom” and the pathways of change for two distinct types of interventions.

**Trial registration:**

ISRCTN12552584, Registered on 13 August 2019.

## Administrative information

Note: the numbers in curly brackets in this protocol refer to SPIRIT checklist item numbers. The order of the items has been modified to group similar items (see http://www.equator-network.org/reporting-guidelines/spirit-2013-statement-defining-standard-protocol-items-for-clinical-trials/).

## Introduction

### Background and rationale {6a}

Research suggests that half of all mental disorders have their onset prior to 14 years of age [1]. In childhood, anxiety and depression seem to be the most common diagnoses [2]. According to recent longitudinal data, the lifetime prevalence of adolescent depression is 11.4%, accompanied by significantly higher risks of adversity through adolescence and adulthood, such as recurrent depression, other mental health issues, lower educational attainment, and relational problems [3]. Depression in adolescence is associated with a five-fold risk of suicide attempts, a two-fold risk of later depression, increased use of psychiatric and medical care, as well as decreased functioning in school, work, family, and social life [4]. Data indicates that merely 13.3% of children with emotional disorders (without comorbid attention-deficity-hyperactivity disorder or behavioural disorders) have been in contact with mental health services [5]. It is therefore of the utmost importance to provide early and preventive interventions for these disorders, which can reach young people who may not otherwise be seen in specialist mental health services.

Accumulating evidence suggests that the effects of psychological interventions delivered via the Internet are comparable to traditional face-to-face treatments [6]. In a meta-analysis of Internet-based interventions for children and adolescents, eleven studies were identified that target psychiatric problems, demonstrating moderate to large effects comparable to those observed in face-to-face psychotherapies [7]. However, the studies’ quality varied substantially, highlighting the need for new high-quality studies in the field [8]. The efficacy of Internet-based cognitive behavioural therapy (ICBT) with added chat sessions for depressed adolescents has been evaluated in two randomized controlled trials (RCTs). In both studies, ICBT was superior to attention control [9, 10].

Cognitive behavior therapy (CBT) and pharmacological treatments are the most established and often recommended treatments for depressed adolescents in many treatment guidelines. However, adverse effects have been linked with pharmacological treatments, including the elevated risk of suicidality [11]. CBT has been extensively researched with robust and reliable effects, but a substantial proportion of adult patients suffering from depression do not gain enough benefit from this form of psychotherapy [12]. Meta-analyses regarding adolescent depression depict a response rate to face-to-face CBT of about 60% [13, 14], and ICBT for mixed disorders in childhood and adolescence between 20% and 76% [7]. Although CBT and ICBT are effective, the significant number of non-responders, along with the factor that offering choice and shared decision-making is an important part of effective health provision, poses two urgent issues to psychotherapy research: (1) the finding of new treatment methods that can complement and/or serve as alternatives to current treatments to effectively treat more patients and (2) the development of methods of detecting non-responders, dropouts, and patients that may deteriorate during treatment (c.f [15].) to enhance, adapt, or alter treatment.

In order to broaden the range of evidence-based therapies available to young people, provide meaningful choice and identify effective treatments for depressed adolescents, more research should focus on treatments that differ from CBT, including psychodynamic psychotherapy (PDT). A meta-analysis of short-term PDT [16] for children and adolescents reported large within-group effects across several outcome domains, with medium to large effects regarding anxiety and mood with continued gains during follow-up; no differences were identified in effectiveness compared to other psychotherapies. These findings have been corroborated by a recent large RCT, where PDT was found to be equally as effective as CBT in the treatment of youth depression [17]. To date, five randomized studies of Internet-based interventions grounded in psychodynamic theory (IPDT) have been published, all of which address adults with mood or anxiety disorders and report medium to large effects compared to control conditions [18–22]. 

### Objectives {7}

This study protocol describes a non-inferiority RCT that will evaluate the efficacy of therapist-assisted ICBT and IPDT for adolescent depression. The study has been preceded by a pilot RCT (*n* = 76) that investigated the efficacy of a novel IPDT treatment for depressed adolescents compared to control condition consisting of weekly symptom follow-up and online supportive contact [23]. The pilot trial showed clinically and statistically significant effects of IPDT compared to control thereby depicting the treatment’s strong acceptability and feasibility. Answering to the need of increased accessibility to digital health interventions, the main goal of the planned study is to further compare the IPDT treatment for depressed adolescents to an established evidence-based treatment (ICBT) in terms of efficacy, cost-effectiveness and factors that affect differential suitability. The primary aim is to examine whether or not therapist-assisted IPDT is non-inferior to therapist-assisted ICBT in treating depression.

#### Primary research question/primary outcome

Is IPDT non-inferior to ICBT in reducing depressive symptoms from pre-treatment to end of treatment in adolescents?

#### Secondary research questions/secondary outcomes

To compare the outcomes of IPDT and ICBT regarding anxiety reduction, emotion regulation and self-compassion.

Data will additionally be collected to make the following secondary analyses in further papers: (1) evaluate and compare cost-effectiveness, (2) identify predictors of outcome, (3) investigate moderators of outcome, (4) examine possible outcome mediators and (5) investigate long term outcome up to 1 year after end of treatment.

### Trial design {8}

The design is a non-inferiority parallel group RCT (*n* = 270). IPDT will be compared to ICBT for adolescents aged 15–19 years with major depressive disorder (MDD). Specific inclusion and exclusion criteria are described under the eligibility criteria. The non-inferiority design tests whether or not IPDT is no less efficacious than ICBT. Eligible participants will be randomized to one of the two arms (1:1 ratio). This non-inferiority RCT will be conducted from 2019 to 2022.

## Methods: participants, interventions and outcomes

### Study setting {9}

The project is based at Stockholm University, Sweden, in close collaboration with Linköping University. As treatment is conducted over the Internet, we will be able to recruit participants across Sweden, which will allow us opportunities for recruiting a larger and more heterogeneous sample regarding several aspects, such as geographic location and socioeconomic status [24]. The project will apply the well-developed infrastructure and the secure and responsive Internet platform developed especially for studies of Internet-based treatments at Linköping University [25].

### Eligibility criteria {10}

Adolescents 15–19 years who have a primary diagnosis of MDD according to DSM-5 [26] are eligible for inclusion. Participants must have access to a computer/smartphone/tablet with Internet connection and be able to read, write, and speak Swedish without the aid of an interpreter. Exclusion criteria include substantial risk of suicide (mainly indicated by clear intent and/or plans reported in the Columbia-Suicide Severity Rating Scale (C-SSRS [27]) interview) and/or earlier suicide attempts, current participation in other psychological treatment, psychotropic medication not stable the last month (or with planned dose adjustments), primary diagnoses other than MDD or current fulfilment of any of the following diagnoses: any psychotic disorder, bipolar I/II disorder, antisocial personality disorder or autism spectrum disorder. Comorbid drug or alcohol abuse is also set as exclusion criteria, whilst withdrawal criteria shall encompass patients who deteriorate such that they become suicidal; these individuals will be withdrawn from treatment and referred to psychiatric care.

The primary depression diagnosis will be established at baseline through telephone interviews using the MINI 7.0 [28]. The MINI can be administered in a short period of time, for which clinical interviewers solely require brief training. Further, suicidality will be assessed with the C-SSRS [27].

#### Therapists

The therapists will be master students recruited from a Swedish clinical programme in psychology (300 credits) in their final phase of psychologist training when they attend their psychotherapy courses. Students who have chosen CBT courses will be recruited as ICBT therapists, whilst students who have chosen PDT courses will be recruited as IPDT therapists. Therapists in the project will be trained in one approach of Internet treatment and supervised weekly by experienced psychotherapists in their respective modalities.

### Who will take informed consent? {26a}

Written informed consent is collected initially and the participants subsequently confirm their consent at two additional occasions. First, participants shall provide their informed written consent in the online application forms prior to screening. Next, participants are given repeated oral study information in the beginning of the diagnostic telephone interview, in which they are encouraged to ask questions, and again asked for consent. The telephone interviewers also ask some follow-up questions to ensure that the participants have understood the basic procedures of the study. Furthermore, after decision to include a participant, prior to randomization, a message is sent to the participant over the secure Internet platform to offer participation in the study, and the participants have to send a reply that confirms their consent to participate. According to Swedish law, parental consent is not needed if the adolescent is ≥ 15 years old, given that the adolescent is able to understand the study information and what participation in the study would mean. Therefore, participants are urged to tell their parents about partaking in the study, but parental consent is not mandatory.

### Additional consent provisions for collection and use of participant data and biological specimens {26b}

No ancillary studies will be undertaken and no biological specimens will be collected.

## Interventions

### Explanation for the choice of comparators {6b}

Internet-based cognitive behavioural treatment (ICBT) is chosen as comparator because its efficacy for adolescent depression has been demonstrated in previous randomized controlled trials. Hence, the experimental treatment, IPDT, is compared to an intervention with established efficacy, ICBT. The main hypothesis is that IPDT will demonstrate non-inferiority to ICBT in reducing depressive symptoms in adolescents with MDD.

### Intervention description {11a}

Both interventions consist of eight therapist-supported self-help modules delivered over 10 weeks on a secure online platform [25]. The modules contain text and videos followed by assignments the patients send to their therapist, receiving feedback within a few days. In addition, participants in both arms of the study will receive 30 min of weekly therapist support via text chat, which was found to be an important ingredient in the empirically supported version of ICBT for adolescents [9, 10]. A guidance protocol (available upon request) has been developed for contact with participants, message frequency and support for handling participants who do not follow their treatment protocols. This guidance protocol is being applied to both treatments to ensure the amount of contact and guidance is comparable in both interventions and further, to ensure the differences amongst the treatments solely regard content and not format.

#### IPDT

The IPDT programme was developed specifically for this project and tested in a pilot RCT [23]. It is based on similar psychodynamic principles as an Internet-based treatment with demonstrated efficacy amongst adults, but adapted to be suitable to adolescents [19, 20, 22]. Through text, videos and a series of experiential exercises, participants are taught how emotional conflicts may underlie and maintain depressive symptoms, how to notice their own anxiety and emotional avoidance (defenses) and how to approach previously warded off feelings. The final part of the programme contains material on how one may express previously warded off emotions to improve important relationships.

#### ICBT

The ICBT programme has previously been evaluated for adolescents suffering from depression [9, 10]. The modules target behavioural and cognitive factors documented to reduce symptoms of depression and anxiety. The treatment programme contains psychoeducation, behavioural activation, cognitive restructuring, affect regulation, anxiety management, and relapse prevention.

### Criteria for discontinuing or modifying allocated interventions {11b}

Criteria for discontinuing is severe psychiatric deterioration during treatment (such as severe suicidality or onset of psychosis) or severe social adversity (such as maltreatment in the family). When there is an indication of such adverse events, the PI (an experienced clinical psychologist) will conduct an assessment over telephone with the adolescent and, if indicated, the parents. The project psychiatrist could also be consulted in these cases. If the participant’s psychiatric deterioration is severe, he/she will be referred to psychiatric care. If the participant is the subject of maltreatment safeguarding standard operating procedures will be followed, including immediately and in accordance with Swedish law reporting this to the local social services for further action.

Allocated interventions could be modified if a participant lacks energy to fulfil all components of the treatment programme. For example, an agreement could be made with the participant to read less of the self-help material or do fewer of the exercises, compared to the full treatment programme. Participants adherence and activity within treatment, i.e. treatment dose, is automatically registered on the treatment platform and will be reported in the trial paper.

### Strategies to improve adherence to interventions {11c}

All participant activity in the programme, such as logging in on the platform, reading modules, completing exercises and attending chats, is automatically recorded on the platform and can thus be monitored and subsequently reported. Participants who miss chat sessions in either arm of the study will receive a text message immediately encouraging them to book a new chat session. Participants that have not had any contact with their study therapist for a full treatment week (i.e. neither completing exercises, writing messages nor attending the chat session) will be contacted by their therapist, initially by text message, thereafter by a phone call. If a participant keeps being nonresponsive for several weeks during the treatment, they will still receive a weekly message from their study therapist.

### Relevant concomitant care permitted or prohibited during the trial {11d}

No concurrent psychological treatment is permitted in order to be included in the trial. Participants are informed that they should not enter concurrent treatment during the treatment phase of the trial. However, if they do so, this is not cause for exclusion from the trial. Participants are asked at post-treatment and all follow-up about any concurrent treatments and this is carefully recorded. Psychotropic medications during the period of treatment are permitted, granted that treatment dose have been stable for at least 1 month prior to enrollment, with no planned dose adjustments during the trial.

### Provisions for post-trial care {30}

If a participant suffers from substantial psychiatric problems at treatment termination or follow-up, he/she will be offered referral to post-trial care at a psychiatric outpatient unit. Any participants who suffer harm from trial participation will be eligible for compensation in line with the rules of Stockholm University’s insurance for research participants at the university (an insurance called “Särskilt personskadeskydd”).

### Participant timeline {13}

See Fig. 1 for a CONSORT diagram of the participant timeline. Participants interested in the project will be directed to an online website where they can access further information about and register for the project, thereby acquiring access to the screening forms for the trial. If fulfilling criteria, and not fulfilling exclusion criteria according to the screening forms, a diagnostic telephone interview will be held to further establish a participant’s fulfilment of the inclusion criteria and non-fulfilment of any exclusion criteria. Eligible participants will be asked to confirm their participation in the study, by electronic written informed consent, thereafter they will be randomized and allocated to treatment.

**Fig. 1 Fig1:**
[figure not shown]
Consort diagram

### Sample size {14}

In order to assess non-inferiority and superiority using a repeated-measures design, power calculations for two-level LMMs were made following Galbraith and Marschner [29] using the R-package powerlmm v. 0.4. A non-inferiority bound of *d* = 0.30 was set alongside an α at 0.05, a variance ratio of 0.75, an attrition rate of 20% and intermittent missing data on weekly measures of 20%. Based on these calculations, a total sample size of 270 is needed to reach 80% power. The power analysis is based on data from the pilot trial [23]. The non-inferiority margin was based on earlier non-inferiority studies comparing face-to-face PDT to CBT in adults suffering from depression, in which Cohen’s *d* = 0.30 was considered as a minimal clinically meaningful difference. Driessen et al. [30] defined non-inferiority as Cohen’s *d* = 0.30 for all continuous outcome measures. Connolly Gibbons et al. [31] defined non-inferiority as 2.5 points on the Hamilton Depression Rating Scale, which was equivalent to a Cohen’s *d* of 0.29.

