## Statistical methods

### Statistical methods for primary and secondary outcomes {20a}

Statistical reporting will follow the CONSORT standards [49]. All participants who are randomly assigned to a condition shall be entered into the main analysis (intent-to-treat analysis = ITT) of the primary outcome measure (QIDS-A17-SR) at the primary assessment point of treatment termination (10 weeks). A secondary analysis of the primary outcome measure will include a per-protocol analysis.

In order to fully explore trajectories of change, a multilevel growth curve level strategy [50] will be employed for measures assessed weekly, comparing estimated change in depressive symptom severity from baseline to end of treatment between groups. Differences in efficacy between conditions will be investigated by modelling interaction effects of group and time. These methods have been recommended for RCTs that investigate Internet interventions [51]. One important advantage is their ability to handle missing data using a maximum likelihood estimation [52]. Non-inferiority will be defined as fulfilled when the upper 90% confidence interval of the estimated QIDS-A17-SR for the IPDT group at treatment termination is below the estimate for the ICBT group plus *d* = 0.30 (i.e. the non-inferiority margin).

The number of patients who changed reliably, as estimated by the Reliable Change Index (RCI [53]), will be reported to provide an estimate of improvement/deterioration in each group that is not attributable to chance. Response will be defined as reliable improvement (i.e. improved more than the RCI), whilst also scoring at least 2 SD below the pretreatment mean. Partial response will be defined as fulfilling the RCI whilst scoring less than 2 SD below the pretreatment mean. Remission will be defined as scoring 6 or below on the QIDS-A17-SR [33].

Secondary outcomes will be analysed primarily according to ITT and with treatment termination as primary assessment point. Mean scores at termination will be compared across groups using analysis of covariance (ANCOVA) controlling for baseline scores.

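### Therapists are nested in arm, but the sample size assumes no therapist variance and the described primary analysis names no therapist effect

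*Protocol article*

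**What the plan says.** **Therapists.** The Therapists section separates the two pools by training: "Students who have chosen CBT courses will be recruited as ICBT therapists", and students on psychodynamic courses become the IPDT therapists. Each is trained in one approach only. No therapist works in both arms.

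**Therapist contact.** Under Intervention description {11a}, "participants in both arms of the study will receive 30 min of weekly therapist support via text chat". Therapists also give feedback on assignments.

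**Sample size {14}.** The section states that "power calculations for two-level LMMs were made" for a repeated-measures design. "A non-inferiority bound of *d* = 0.30" "was set alongside an α at 0.05, a variance ratio of 0.75", with 20% attrition and 20% intermittent missing data. On that basis "a total sample size of 270 is needed to reach 80% power". No therapist ICC, caseload or design effect is among the inputs.

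**Primary analysis {20a}, {20c}.** The model is a multilevel growth curve fitted as a linear mixed model: "Differences in efficacy between conditions will be investigated by modelling interaction effects of group and time". The number of levels is not stated and no therapist term is named. The decision uses the upper limit of a 90% interval: "Non-inferiority will be defined as fulfilled when the upper 90% confidence interval of the estimated QIDS-A17-SR for the IPDT group at treatment termination" must lie below the ICBT estimate plus the margin. The Discussion says that the power analysis took the planned multilevel modelling into account.

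**The concern.** Participants who share a therapist may have correlated outcomes. Therapist contact is part of both treatments, and the protocol measures alliance every week as a possible mediator, so it treats the therapist relationship as something that could drive change in depression scores. Because no therapist works in both arms, differences between therapists do not cancel within therapist. They enter the comparison of arms directly.

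A two-level model, with measurements within participants, counts all participants as independent. Two things are then at stake:

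- **Power.** The sample size allows for no between-therapist variance.
- **Error rate.** If the analysis also omits therapist, its standard error is too small. In a non-inferiority trial this is the harmful direction, because a narrow interval clears the margin more easily.

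**Working it through.** **Inputs from the protocol.** Margin d = 0.30; α 0.05, taken as one-sided because the decision uses a 90% interval; power 80%; N = 270, 1:1, so 135 per arm; 20% attrition and 20% intermittent missing data; variance ratio 0.75.

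**Inputs assumed.** Participants per therapist (m) and therapist ICC are not given. Here ICC means the share of the variance of the quantity compared between arms (a participant's estimated change) that lies between therapists.

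**Step 1: the plan's own figure.**

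- The simple two-means formula gives 2 × (1.645 + 0.842)² / 0.30² = 137.4, so 138 per arm and 276 in total before attrition. With 20% attrition it gives 276 / 0.8 = 345.
- A two-level growth model with 11 weekly points, variance ratio 0.75 (taken as slope to error variance), the stated missingness and N = 270 gives 77.5% to 78.6% power at one-sided 0.05 when d is scaled by the end-point SD. Scaled by the slope SD it gives about 77%, and by the pre-treatment SD only 9% to 14%.
- The figure of 270 is therefore roughly consistent with a two-level, one-sided 0.05 calculation without a therapist component. It cannot be reproduced uniquely, because the baseline ICC, the standardiser for d and the definition of the variance ratio are not stated. From here on, 80% power at N = 270 is taken as given.

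**Step 2: effect of therapist.** The design effect is DE = 1 + (m − 1) × ICC. The true standard error is √DE times the one that ignores therapist. There are two possible analyses:

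- *Therapist ignored:* type I error = Φ(−1.645/√DE); power = Φ(0.842/√DE).
- *Therapist modelled:* type I error about 5%; power = Φ(2.486/√DE − 1.645), where 2.486 is 1.645 + 0.842 before rounding.

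Example for m = 8, ICC 0.05: DE = 1 + 7 × 0.05 = 1.35 and √DE = 1.162. Ignored: Φ(−1.416) = 7.8% error, Φ(0.724) = 77% power. Modelled: Φ(2.140 − 1.645) = Φ(0.495) = 69% power.

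| m | ICC | DE | Ignored: type I error | Ignored: power | Modelled: power (error about 5%) |
|---|---|---|---|---|---|
| any | 0 | 1.00 | 5.0% | 80% | 80% |
| 5 | 0.01 | 1.04 | 5.3% | 79.5% | 78.6% |
| 8 | 0.02 | 1.14 | 6.2% | 78.5% | 75.3% |
| 8 | 0.05 | 1.35 | 7.8% | 76.6% | 69.0% |
| 8 | 0.10 | 1.70 | 10.4% | 74.1% | 60.3% |
| 10 | 0.05 | 1.45 | 8.6% | 75.8% | 66.3% |

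A simulation with 17 therapists of 8 participants per arm, analysed without therapist, gave type I error of 6.2%, 7.9% and 10.3% at ICC 0.02, 0.05 and 0.10, in line with the formula.

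**The case against.** **The random-effects structure may be left to the analysis plan.** The words two-level appear only in the power calculation. The analysis sections say multilevel and linear mixed model, without listing levels, and a separate analysis plan could add therapist. This stands. A reader might infer that the primary model is certainly two-level; the link in the Discussion makes that plausible, but the protocol does not say it. What the protocol does fix is the power assumption. Adding therapist later would repair the interval, but N = 270 would still have been set without that variance.

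**Therapist variance may be small.** Both arms use self-help modules, a common guidance protocol governs contact and message frequency, and therapists are supervised weekly. These features could hold the ICC down, and they make 0.10 an upper illustration, not an expectation. They do not show that it is zero.

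**The size is not documented.** A reader might infer as fact that the interval is too narrow and that 80% power is not delivered. Neither follows without an ICC and a caseload.

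**Inflated error and the full power loss do not occur together.** It is tempting to pair, say, 7.8% error with 69% power. The first belongs to an analysis that ignores therapist, whose power is about 77%. The second belongs to one that models it, whose error is about 5%.

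**The scale of the ICC matters.** If it were defined as a share of the true slope variance, residual error and missing data would dilute it, and the design effects above would be too large.

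**Conclusion.** The point holds in conditional form. Therapist is nested in arm, the sample size sets therapist variance to zero, and the described primary analysis names no therapist effect. For any positive ICC, with more than one participant per therapist, the stated 80% is optimistic. If therapist is also left out of the analysis, the deciding interval errs in the anti-conservative direction.

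The size ranges from negligible (ICC 0.01 with 5 per therapist) to material. At 8 per therapist and ICC 0.05, the error is nearly 8% if therapist is ignored, or about 11 points of power are lost if it is modelled. This rests on an assumed ICC and caseload, on 80% at N = 270 being correct without clustering, on a one-sided 0.05 test and on normal approximations. It is more than missing detail, because it bears on the interval that decides the trial's main claim.

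**What to change.** Before the masked analysis:

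1. In the primary mixed model, specify a therapist-level random effect on the time slope, with therapist nested in arm, and a small-sample degrees-of-freedom correction such as Kenward-Roger or Satterthwaite.
2. Add a therapist random effect to the models for the secondary outcomes.
3. Give analysts neutral therapist codes, prepared when the database is masked for arm.
4. State the number of therapists and the actual caseload, and restate power over a range of therapist ICC, for example 0, 0.02 and 0.05. Keep N = 270.

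**Cost.** No new data collection should be needed, since the Implementation section {16c} has each participant assigned to a named study therapist. The price is a somewhat wider interval, a less favourable power figure, and a coding step so that therapist codes do not unmask the analysts. Fixing the term now matters, because adding it after results are seen would be a post hoc choice on the primary decision.
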